#### Costs

To investigate the influence of the Blue Care ICA on per capita costs, two levels for computing reimbursements retrospectively are distinguished: population level and user level. First, the amount and the trend in the annual reimbursements during the intervention period (T0-T3) in the health and social care domain (care and support financed under the Health Insurance Act by the health insurance company and the Social Support Act/Youth Act/Participation Act/Public Health Act by municipalities) are computed on a population level for the citizens in the four neighbourhoods where the Blue Care ICA is being implemented (total amount as well as mean per citizen). These reimbursements will be compared to the reimbursements in the reference period 2015–2016 and to the comparison neighbourhoods (risk –adjusted standardized reimbursements) as well as the national figures to investigate whether a break in the trend of increasing costs will appear at the population level. Furthermore, the annual mean volumes of used medical services and services in the social care domain will be computed for both the intervention and comparison neighbourhoods to investigate whether changes in the number of used services took place (user level).

Health care costs with data related to health and social care, as well as reimbursement data will be collected via existing databases and registration systems from the health insurer VGZ, the municipality of Maastricht, and Statistics Netherlands (CBS, national statistics database with an overview of volumes and costs of both health as social care).

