#### Citizens in action

The first core element aims to change citizens’ attitude, self-efficacy and behavior to give meaning to their own lives and stimulate societal participation (‘citizens in action’). Citizens are actively involved in Blue Care and are stimulated to address bottlenecks and develop projects which address these bottlenecks. Recent findings in the intervention neighbourhoods from the perspective of the citizens showed that there is a lack of communication between health and social care professionals, there is too much bureaucratic delay, and rules and regulations are considered to be inflexible with insufficient attention to the needs of citizens. In addition, citizens are consulted on a regular base during Blue Care by a citizen panel which comes together two times a year facilitated by the researcher and a member of the Blue Care coordination team. Hence, these meetings serve both as a research and a practical implication tool to diminish the burden on the citizens.

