#### Combining budgets

The third core element, ‘combining budgets’, will build a reimbursement system in which the budgets for health and social care are combined on a population level. Therefore, the budgets of the dominant health insurer in the south of Limburg (VGZ, Health Insurance Act) will be combined with the budgets of the social care domain (Social Support Act, Youth Act and Participation Act).

The financial reimbursement system is agreed upon at the macro (policy) level and is considered to be a prerequisite for enabling and facilitating the implementation of initiatives at the micro and meso (community and organizational) level. The national budgets of the Long –Term Care Act will not be included in the budget of the Blue Care ICA, even though the costs in this area will be monitored along the way. The objective is that the costs of health and social care, following the implementation of projects within the Blue Care ICA, will be in accordance with available financial budgets (thereby breaking the trend of increasing costs) or, ideally, that projects will lead to a decrease in costs. To judge this, the reimbursements of 2015 in these domains will be used as an upper limit.

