• Citizen needs of the people living in the intervention neighbourhoods, • The influence of external policies on the Blue Care ICA	- Does the ICA meet the needs of the citizens and professionals living and working in the neighbourhoods? - Are there other contextual or environmental features which play a role in the experienced quality of life of citizens living in the neighborhood? - How do external strategies (policy and regulations / government) influence the pilot and the implementation?	Citizens: Citizen panel *n* = 10 × 2 (1 panel per two neighbourhoods) Policy: observations during existing board and financial sponsor meetings	Citizen Panel: T1, T2, T3 (meet 2 times a year) Policy: T0, T1, T2, T3 (ongoing between 2017 and 2020)
• Governance structure of the Blue Care ICA	- How is the governance model structured, how does this develop in these four years and what are the different roles in this structure (leadership, champions etc.)?	Observations during existing board and financial sponsor meetings, semi-structured interviews	T0, T1, T2, T3 (ongoing between 2017 and 2020)
• Implementation of the bottom up approach, • Collaboration, interaction and communication on macro, meso and micro level, • Use and implementation of Positive Health by health and social care professionals	- How are citizens and professionals actively involved and attracted in the pilot process (goal is bottom – up approach)? - How do healthcare and social service providers collaborate in the social domain at macro, meso and micro level and to what extent are they able to prioritize mutual interests above their own organisational interests? - How do professionals deliver person-centred care and support from a generalist perspective according to the principles of Positive Health, how do they implement Positive Health into their daily routine, and what is the influence on the type of care and support provided to citizens?	Participant observations at all levels, analyzing meeting notes, semi-structured interviews, focus groups with health and social care professionals, citizen panel	T0, T1, T2, T3 (ongoing between 2017 and 2020)

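### The cost aim is framed as per capita costs but measured as reimbursements, so any ICA running cost booked outside the listed acts is missed, on the intervention side only

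*Protocol article*

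**What the plan says.** The protocol article words the cost aim in two ways.

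- **As per capita costs.** Study design lists lower per capita costs among the aims. The Costs section opens in the same terms: "To investigate the influence of the Blue Care ICA on per capita costs, two levels for computing reimbursements retrospectively are distinguished: population level and user" […]. It then looks for a break in the upward cost trend. Combining budgets wants costs to stay within the available budgets "or, ideally, that projects will lead to a decrease in costs".
- **As reimbursements.** The research question asks about changes in total reimbursements and substitution between types of reimbursement. Combining budgets takes the 2015 reimbursements as the ceiling.

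The measurement follows the second wording. The Costs section counts "care and support financed under the Health Insurance Act by the health insurance company" and, on the municipal side, "Social Support Act/Youth Act/Participation Act/Public Health Act by municipalities". It adds mean volumes of services used. The data come from "existing databases and registration systems from the health insurer VGZ, the municipality of Maastricht, and Statistics Netherlands". Data analysis plans descriptive statistics on total reimbursement and on its split between the social and health care domains.

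The article also mentions resources that belong to the ICA itself. The citizen panel is "facilitated by the researcher and a member of the Blue Care coordination team". Table 3 under Process evaluation lists "Policy: observations during existing board and financial sponsor meetings". Sub-projects are developed as implementation proceeds. Neither the Costs section nor Data analysis names ICA programme accounts or a programme-cost component.

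**The concern.** Reimbursement and cost are the same quantity only if everything the ICA spends passes through one of the listed acts. Spending that does not is absent from the intervention neighbourhoods' figure. The comparison neighbourhoods do not implement the approach and so have no matching item, which means the omission can only favour the intervention. The same holds against the 2015 ceiling and the national figures, to the extent that these contain no ICA spending.

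Substitution makes this more relevant, since it is itself a research question. If care moved from a reimbursed service into a sub-project paid for outside the acts, the reimbursed part would disappear and its replacement would not be counted. At stake is the meaning of the answer on one of the four Quadruple Aim goals: a finding about payer reimbursements could be read as a finding about what the population's care costs.

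**Working it through.** The article states no saving, programme budget or per capita cost, so there is no figure of its own to reproduce. The check shows what the measure captures and how large a gap could be.

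**Inputs**

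- Inhabitants of the intervention neighbourhoods (Table 1): Nazareth 3,280; Limmel 2,370; Wyckerpoort 4,015; Wittevrouwenveld 5,706.
- ICA running cost: not given, so assumed over a range.
- Share of running cost already booked under the listed acts: not given, so varied from 0 to 1.

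**Step 1: cost per citizen of spending left uncounted**

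Inhabitants = 3,280 + 2,370 + 4,015 + 5,706 = 15,371.

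| Assumed uncounted spending per year (EUR) | Divided by 15,371 (EUR per citizen per year) |
|---|---|
| 100,000 | 6.51 |
| 250,000 | 16.26 |
| 500,000 | 32.53 |
| 1,000,000 | 65.06 |

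**Step 2: when the reported direction is wrong**

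Per citizen per year, let *s* be the gross saving in reimbursements, *c* the ICA running cost, and *f* the share of *c* already booked under the listed acts.

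- Reported change = −*s* + *f* × *c*
- Full change = −*s* + *c*
- Full minus reported = (1 − *f*) × *c*, which is never negative

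A reduction is reported while full cost rises only when *f* × *c* < *s* < *c*.

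**Step 3: illustration with assumed amounts (EUR per citizen per year)**

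| *s* | *c* | *f* | Reported change | Full change |
|---|---|---|---|---|
| 50 | 60 | 0 | −50 | −50 + 60 = +10 |
| 50 | 60 | 0.5 | −50 + 30 = −20 | +10 |
| 50 | 60 | 1 | −50 + 60 = +10 | +10 |
| 50 | 30 | 0 | −50 | −50 + 30 = −20 |

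The first two rows give the wrong direction. In the third, all running cost is booked under the acts and there is no error. In the fourth the direction is right but the reduction is overstated by EUR 30. For scale, *c* = 60 corresponds to 60 × 15,371 = EUR 922,260 a year. The article gives none of *s*, *c* and *f*, so it does not determine which row applies.

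**The case against.** The strongest reply is that running costs may already be counted. Combining budgets pools the insurer's and the social-domain budgets, calls that pooling a precondition for the initiatives, and wants costs after the projects start to fit within the budgets. If sub-projects and coordination are paid that way and appear in the payers' records, *f* is near 1 and nothing is missing. This stands as a real possibility. It does not settle the matter: the combined budget is still to be built, its implementation is an open process question, and the article nowhere says that it pays for the coordination team or the sub-projects.

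Second, the research question and the 2015 ceiling are both in reimbursements, and the analysis is descriptive, with no net-saving or cost-effectiveness claim planned. Counting reimbursements does answer that question. It does not answer the per capita cost aim in Study design and Costs, and a descriptive comparison can still mislead if labelled as cost.

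Third, the Costs section mentions cost data as well as reimbursement data, and the full protocol may say more. That is fair, but the sources named are payer and national statistics records, with no programme accounts among them.

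A reader might also take the mention of financial sponsors to mean that sub-projects are funded outside the acts. The article does not say who these sponsors are or what they fund. They could be the insurer and the municipality, whose spending is counted.

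**Conclusion.** The mismatch is in the text: the aim is worded as per capita costs, while the measure is reimbursements under five acts plus service volumes. Any ICA running cost outside those acts is left out on one side only, in the direction that favours the intervention.

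Its size and its effect on the conclusion are unknown. Each assumed EUR 100,000 a year not counted is EUR 6.51 per citizen per year, using the Table 1 populations. There is no expected saving or per capita reimbursement level in the article to compare this with.

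A reader might go further and infer that a programme costing more than it saves would be reported as reducing per capita costs. The documents do not support that. It requires the saving to lie between the running cost already counted and the full running cost, and none of these is stated. If all running cost passes through the listed acts, the problem disappears. The supported conclusion is that such a report could occur and that the plan as described has no step to detect it.

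**What to change.** In the Costs and Data analysis sections:

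1. State how the coordination team and the sub-projects are funded.
2. Identify ICA programme spending not already booked under a listed act, excluding research costs, and check it against the combined budget so that nothing is counted twice.
3. Show start-up and recurring costs separately. The article places the starting phase in 2016, within the 2015–2016 reference period, so some start-up spending may fall before the intervention years.
4. Report this spending per inhabitant per year beside reimbursements, with the net total, for the intervention neighbourhoods.
5. Base any statement about per capita costs on the net total. If programme cost cannot be obtained, label the outcome as reimbursements and limit the conclusion to them.

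The cost is a small amount of accounting work: annual programme accounts from the coordination team and the funders, and additional lines in the cost table. The researchers already plan to observe the board and sponsor meetings, which should help in obtaining the accounts. The cost figure may turn out less favourable to the intervention.

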#### Work satisfaction of professionals

Work satisfaction of the professionals in the neighbourhoods and the facilitators and barriers for the implementation of Positive Health within daily working routines will be investigated. Both overall work satisfaction and work satisfaction during the specific sub-projects will be investigated. Data will be collected using semi-structured interviews with health and social care professionals in the neighbourhoods. A wide range of social care professionals (e.g.: general practitioner, nurse, social care worker) will be interviewed to get a broad understanding of the facilitators and barriers.

### Sample size considerations effect measure

The sample size calculation for the study is based on the primary outcome measure health-related quality of life, measured with the SF-12v2. To demonstrate a clinically relevant treatment difference of 3.0 on the Mental Component Summary Scale Score, given SD = 8.88 [36], and an alpha of 0.05 and a power of 0.80, the minimally required number of participants is 138 per study. In order to demonstrate the effects of the ICA on the subpopulation level with respect to age (18–65 years vs. 65 years and older), 138 participants per age category are required, resulting in a total of 2 × 138 = 276 participants per study group. The total required sample size (intervention + comparison group) is therefore 552 (2 × 276).

It is expected that 15% of all citizens approached for participation by means of an information letter and consent form will agree to participate. Additionally, a drop-out rate of 50% between T0 and T3 is expected. Accounting for drop-out, 1104 citizens need to be enrolled at T0 (552 per study group). Based on the expected response rate of 15% across all age groups and neighbourhoods, 7360 citizens (3680 per study group) need to be approached for participation. As the required number of participants to be approached per study group closely resembled the number of clients in the general practice population that were eligible for inclusion (at least for the comparison group), we decided to approach all eligible citizens to prevent selection bias. Figure 4 presents a flow chart of the study based on the actual number of citizens approached for participation, the expected response rate and the expected drop-out rate.

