### Target population

The target population of the Blue Care ICA is all citizens who reside in the participating neighbourhoods. Additional inclusion criteria for the study are that citizens should have resided in the neighbourhoods for at least 3 years and should be at least 18 years of age.

The intervention group comprises the four neighbourhoods in which the Blue Care ICA is implemented. A comparison group was selected based on similarity of the ‘comparison’ citizens with their ‘intervention’ counterparts in terms of demographic neighbourhood characteristics (socioeconomic status, ethnicity, use of health and social care domain).

In the intervention neighbourhood, two general practices are located and both agreed to participate in this study.

Of the five general practices located in the comparison neighbourhoods, two general practices agreed to participate in this study. Reasons for non-participation were: not enough time for potential extra tasks and fear of burdening their patients with possibly unwanted questionnaires. All general practices (comparison and intervention) are group practices.

Citizens living in the intervention and comparison neighbourhoods were selected from the Electronic Patient System (EPD) of the participating general practices located in these neighbourhoods. Citizens eligible for participation in the study approached by means of a information letter and consent form, accompanied by a letter from their general practice. Signed consent forms are obtained from all citizens willing to participate in the study.

Table 1 shows the demographic characteristics of the intervention and comparison neighbourhoods [17, 30–32]_._ The age distribution in the intervention neighbourhoods is equal to the average of the comparison neighbourhoods, except for a somewhat higher proportion of those under age 25 (mostly student population, 18–24 yrs) and a lower percentage of people over 65 years in the intervention neighbourhoods. The inhabitants of the intervention neighbourhoods feel slightly more in control over their life compared to the comparison neighbourhoods.

**Table 1 Tab1:** Demographic characteristics of intervention and comparison neighbourhoods

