### Data analysis

Descriptive statistics will be computed to describe the characteristics of the target population in participating neighbourhoods (e.g., age, socioeconomic status, ethnicity, household composition) and to compare the intervention and comparison neighbourhoods at baseline. Relevant statistical tests (e.g., t-test, chi-square, analysis of variance, regression analysis) will be applied to analyse effects on the primary and secondary outcome measures (level of significance is 0.05; two-tailed). Data will be analysed according to the intention-to-treat principle. This means that all subjects included in the intervention group will be analysed as intervention subjects irrespective of whether they received the intervention or not. This allows for judging whether the neighbourhood population as a whole benefits from the Blue Care ICA, irrespective of whether citizens actually received (elements of) the intervention.

In all analyses, possible baseline differences between citizens from intervention and comparison neighbourhoods will be corrected for. In addition, subgroup analyses will be performed to investigate whether certain groups of citizens benefit more from the integrated community approach than others (i.e., according to age, gender, type of problems, socioeconomic status). Qualitative data will be analysed using narrative descriptions of procedures and meetings, identifying themes in the focus group with professionals, citizens’ panels, and semi-structured interviews with citizens, professionals, managers, and directors. Interviews will be transcribed verbatim and Nvivo 12.0 will be used for the analysis.

Descriptive statistics will be used to describe the total amount of reimbursement at the population level over time as well as (changes in) the proportion of reimbursement in the social domain (on account of the Social Support Act, the Youth Act and the Participation Act) and in the health care domain (on account of the Health Insurance Act, e.g., primary care, hospital care, mental health care, medication and diagnostics).

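### The sample size of 138 per age category assumes independent citizens although exposure is by whole neighbourhood, so on the plan's own inputs the stated power of 0.80 per age category is not delivered once citizens are correlated

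*Protocol article*

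**What the plan says.** Protocol article, Sample size considerations effect measure: the target is a "clinically relevant treatment difference of 3.0 on the Mental Component Summary Scale Score" with SD 8.88. The result is "an alpha of 0.05 and a power of 0.80, the minimally required number of participants is 138 per study" group. Because effects are to be shown in two age categories, the number is doubled, "resulting in a total of 2 × 138 = 276 participants per study group", which gives 552 in total. It is then increased for 50% drop-out (1104 enrolled) and 15% response (7360 approached). No ICC, design effect or number of neighbourhoods enters at any step.

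Target population: "The intervention group comprises the four neighbourhoods in which the Blue Care ICA is implemented". Table 1 lists four comparison neighbourhoods. Participants come from the records of general practices. Both practices in the intervention area take part; on the other side, "Of the five general practices located in the comparison neighbourhoods, two general practices agreed to participate in this study".

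Data analysis: "Relevant statistical tests (e.g., t-test, chi-square, analysis of variance, regression analysis) will be applied to analyse effects on the primary and secondary outcome measures", with the "level of significance is 0.05; two-tailed". Baseline differences between the two sets of citizens are to be corrected for in all analyses. The declared purpose of the intention-to-treat analysis is to judge benefit for the neighbourhood population as a whole.

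**The concern.** Citizens of one neighbourhood share its housing, services, practices and local policy, so their scores tend to be correlated. A comparison of four neighbourhoods with four others then carries less information than the same number of unrelated citizens. It also has only eight units from which to judge how much neighbourhoods differ when the programme has no effect.

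Two things are at stake. The 0.80 is a planning claim about the age-category comparisons, and it has no slack for clustering. And if the final tests also ignore neighbourhood, standard errors are too small, and a local change unrelated to Blue Care may be reported as an effect.

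Table 1 gives a reason to expect some clustering on a related measure: within the intervention group alone, increased risk of anxiety or depression ranges from 36% to 69% between neighbourhoods. This is only indicative, because the survey numbers behind those percentages are not given.

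**Working it through.** **Inputs from the article.** Difference 3.0; SD 8.88; two-sided alpha 0.05; power 0.80; 138 per group per age category; 276 per group in all; 4 + 4 neighbourhoods; 2 + 2 practices.

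**Assumptions.** ICC of 0.001 to 0.02 at neighbourhood level; equal numbers per neighbourhood (138/4 = 34.5 and 276/4 = 69). The article gives neither.

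**1. The plan's figure.** n per group = 2 × (1.960 + 0.842)² × 8.88² / 3.0² = 137.5, rounded up to 138. Power at 138 is 0.801. The design effect is therefore exactly 1. The only slack is rounding: 138/137.54 = 1.0034, which is used up at an ICC of 0.0034/33.5 = 0.0001.

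**2. Power with clustering, no baseline adjustment.** Design effect DE = 1 + (m − 1) × ICC; SE = 8.88 × √(2 × DE / n). Power is taken from the normal distribution at 3.0/SE, and from the non-central t with 8 − 2 = 6 degrees of freedom. Example, age category at ICC 0.01: DE = 1 + 33.5 × 0.01 = 1.335; SE = 8.88 × √(2.67/138) = 1.235; 3.0/1.235 = 2.43; power 0.68 (normal) or 0.53 (6 df).

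| ICC | Age category (138): DE | Normal | 6 df | Whole group (276): DE | Normal | 6 df |
|---|---|---|---|---|---|---|
| 0.001 | 1.03 | 0.79 | 0.64 | 1.07 | 0.97 | 0.89 |
| 0.005 | 1.17 | 0.74 | 0.59 | 1.34 | 0.93 | 0.81 |
| 0.01 | 1.34 | 0.68 | 0.53 | 1.68 | 0.86 | 0.72 |
| 0.02 | 1.67 | 0.58 | 0.45 | 2.36 | 0.73 | 0.58 |

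Under independence the whole-group comparison has power 0.978. It crosses 0.80 at an ICC of about 0.015 (normal) or 0.005 (6 df).

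**3. Limit on adding citizens.** With four neighbourhoods per group, the effective number per group cannot exceed 4/ICC. Setting this equal to 137.5 gives ICC = 4/137.5 = 0.029. From there on, no number of citizens reaches 0.80, even by normal approximation.

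**4. With the baseline score as covariate.** The SD becomes 8.88 × √(1 − r²). The article gives no correlation r; assume 0.5 to 0.6 with the ICC unchanged, so the SD is 7.69 to 7.10. At ICC 0.01 on 6 df, power is 0.65 to 0.72 per age category and 0.84 to 0.89 for the whole group. By normal approximation with r = 0.5 the age-category figure is about 0.80 (SE = 7.69 × √(2.67/138) = 1.070; 3.0/1.070 = 2.80).

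**5. Level of a test with no neighbourhood term.** True two-sided level = 2 × (1 − Φ(1.96/√DE)). At ICC 0.005 / 0.01 / 0.02 it is 7% / 9% / 13% per age category and 9% / 13% / 20% for the whole group. Simulation at ICC 0.01 and 0.02 gave 9.2% and 13.1% for 138 per group, and 13.0% and 20.4% for 276 per group.

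**6. Practice as the cluster.** With two practices per group, 138 per group and ICC 0.01, DE = 1 + 68 × 0.01 = 1.68; power is 0.58 by normal approximation and the unadjusted level is 13%.

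**The case against.** Several points on the other side are sound.

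- **The test list is illustrative.** It is introduced by e.g., regression does not exclude a multilevel or cluster-robust model, and an analysis plan not shown here may name one. A reader might infer that the plan will exceed its 0.05 level. The article does not support that as a flat statement: the excess arises only if the tests are run with no neighbourhood term.
- **The whole-group comparison is not generally underpowered.** A reader might infer that the entire study misses 0.80. It does not at low ICC, as the table shows.
- **Baseline correction is promised.** The unadjusted figures are pessimistic if the baseline score is a covariate. Correction may also remove stable neighbourhood differences. It does not remove neighbourhood-specific change over the follow-up period, which is what can pass for an effect.
- **The ICC is assumed.** At 0.001 the age-category loss is trivial by normal approximation (0.79), and the unadjusted level is 5.4%.
- **Six degrees of freedom cost power even at ICC 0** (0.65 per age category). That is the price of the cautious reference distribution. With no clustering the independent-citizens calculation is right, so this is not a fault of the plan.

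What these points do not reach is the sample-size statement itself. The article fixes 138 and 0.80 with no allowance for clustering and does not use baseline adjustment to justify them. A later choice of model cannot make that calculation describe a design of eight neighbourhoods. Approaching all eligible citizens helps only within the limit in step 3 of the working.

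**Conclusion.** The point holds in a limited form. The arithmetic of 138 is correct; the independence assumption behind it does not fit exposure by neighbourhood. On the plan's own inputs, the stated power per age category is not delivered for any positive ICC beyond the rounding margin.

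The direction is certain; the size is not. For ICCs of 0.005 to 0.02, with equal neighbourhoods and no baseline adjustment, power per age category is 0.74 to 0.58 (normal) or 0.59 to 0.45 (6 df). Unequal neighbourhood sizes would worsen this, and a baseline covariate would improve it. The whole-group comparison is affected only above the thresholds given in the working. The error-rate concern is conditional on an analysis without a neighbourhood term, which the article neither commits to nor rules out.

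**What to change.** In Data analysis, state that effects are estimated with a mixed model that has neighbourhood as a random effect, the baseline score as covariate and small-sample degrees of freedom (Kenward-Roger or Satterthwaite), with general practice as the clustering level in a sensitivity analysis.

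In Sample size considerations, replace the single 0.80 by the power achievable with 4 + 4 neighbourhoods over a stated ICC range, separately for the age categories and the whole group. State the assumed baseline correlation if the adjustment is counted.

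A permutation analysis at neighbourhood level is at most an optional sensitivity check, because the Discussion makes clear that neighbourhoods were not assigned at random.

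The cost is wording, a less favourable stated power and wider intervals. No extra enrolment is needed, but the change does not restore 0.80 in the age categories. It makes the claim match the design, and readers should interpret the age-category results accordingly.

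### The sample size needs half of each group's completers to be 65 or older, but unstratified recruitment in neighbourhoods with 11–28% of residents aged 65+ does not supply them, so the 0.80 power is not supported for older citizens

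*Protocol article*

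**What the plan says.** In the Protocol article, Sample size considerations effect measure, the calculation targets a "clinically relevant treatment difference of 3.0 on the Mental Component Summary Scale Score", with SD 8.88 and "an alpha of 0.05 and a power of 0.80", giving 138 per group. The number is then doubled in order to show effects at the "subpopulation level with respect to age (18–65 years vs. 65 years and older"). The doubling itself is worded "138 participants per age category are required, resulting in a total of", which the article works out as 276 for each group and 552 overall.

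From there the age categories disappear. A single 50% drop-out takes 276 to 552 enrolled per group, and a single response rate takes that to 3680: "Based on the expected response rate of 15% across all age groups and neighbourhoods, 7360 citizens (3680 per study group) need to be approached". The section adds that this number was close to the eligible practice population, at least for the comparison group, and that everyone eligible would be approached.

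Target population notes "a lower percentage of people over 65 years in the intervention neighbourhoods", and Table 1 gives the age bands for each neighbourhood. Data analysis sets the test as "level of significance is 0.05; two-tailed" and says that "subgroup analyses will be performed to investigate whether certain groups of citizens benefit more from the integrated community approach than others", with age among the listed groupings.

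**The concern.** Doubling 138 to 276 gives 138 older completers only if older people make up half of those who finish. When everyone is approached and all ages respond and drop out at the same rates, completers have the age mix of the people approached. Table 1 shows no neighbourhood near one half.

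Demonstrating effects by age is the only reason given for doubling the sample. If the older stratum is far smaller than planned, the extra recruitment mostly enlarges the younger stratum. A non-significant result at 65+ could then sit beside a significant result in younger adults simply because the strata differ in size. Readers who trust the stated 0.80 might take that as evidence that older citizens do not benefit.

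**Working it through.** **1. The plan's own figures reproduce.** n = 2 × (1.96 + 0.84)² × 8.88² / 3.0² ≈ 137.5, so 138 per group; the two-sample t-test power at 138 is 0.80. Then 2 × 138 = 276; 276 / 0.50 = 552; 552 / 0.15 = 3680 per group.

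**2. What 138 older completers would require.** Planned yield = 0.15 × 0.50 = 0.075 completers per person approached. 138 / 0.075 = 1840 people aged 65+ approached per group, which is 50% of 3680.

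**3. Residents by age band (Table 1 percentages × inhabitants).**
- Intervention, 65+: 0.16×3280 + 0.12×2370 + 0.20×4015 + 0.11×5706 ≈ 2240. In the same way, 25–64 ≈ 7838 and 0–24 ≈ 5293.
- Comparison, 65+: 0.17×4965 + 0.22×2415 + 0.17×3410 + 0.28×5345 ≈ 3452. In the same way, 25–64 ≈ 8124 and 0–24 ≈ 4573.

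**4. Share of adults aged 65+.** Table 1 does not split the 0–24 band at 18, so let f be the adult fraction of that band. This is an assumption, run from 0 to 1. Share = 65+ / (65+ plus 25–64 plus f × 0–24).

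**5. Completers and power.** Completers aged 65+ = 276 × share. SE = 8.88 × √(1/n₁ + 1/n₂). Power is from the two-sided two-sample t-test at 0.05, unadjusted, for a difference of 3.0.

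| f | 65+ share, int. / comp. | 65+ completers, int. / comp. | SE | Power, 65+ | Detectable at 80% | Power, younger stratum |
|---|---|---|---|---|---|---|
| 0 | 22.2% / 29.8% | 61 / 82 | 1.50 | 0.51 | 4.2 | 0.93 |
| 0.5 | 17.6% / 24.9% | 49 / 69 | 1.66 | 0.43 | 4.7 | 0.94 |
| 1 | 14.6% / 21.4% | 40 / 59 | 1.82 | 0.37 | 5.1 | 0.95 |

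**6. Sensitivity to the 3680 and to the age mix (unadjusted).**
- Intervention list twice as long (80–123 completers aged 65+), comparison unchanged: power 0.50–0.66.
- All 2240 older intervention residents approached (2240 × 0.075 = 168 completers), comparison unchanged: 0.60–0.71.
- Each group given the age mix of its oldest neighbourhood with f = 0 (Wyckerpoort 20/69 = 29%, Malberg 28/78 = 36%): 80 and 99 completers, power 0.61.
- Yield among older citizens needed to reach 138 from 3680: 12.6–17.5% (comparison) and 16.9–25.7% (intervention), against the planned 7.5%.

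**7. Whole-group comparison.** With 276 per group, power for 3.0 points is about 0.98.

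**The case against.** Several points on the other side have force.

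- **Intervention list length.** Everyone eligible was approached, and the match to 3680 is claimed only for the comparison group. The actual numbers are in Figure 4, which is not shown. A reader might infer that neither group can reach 138 older completers. The documents support that only for the comparison group, whose eligible list is about 3680.
- **Table 1 is not the sampling frame.** It counts all residents, whereas citizens come from the lists of two intervention and two of five comparison practices, with at least 3 years' residence. That rule may remove students and raise the older share. The oldest-neighbourhood check covers a good part of this and still gives only 0.61.
- **The power figures are unadjusted.** Data analysis says baseline differences will be corrected for. If that means adjusting for the baseline score (assumption; no correlation is given), the SD shrinks by √(1 − ρ²). With ρ = 0.5–0.7, the 65+ power at 3680 per group becomes about 0.47–0.80. With ρ = 0.7 and a doubled intervention list it is about 0.78–0.91. Clustering would pull the other way. So 0.37–0.51 is not the power of the final analysis. It is the figure on the same unadjusted basis as the plan's 138 and 0.80, and on that basis the shortfall stands.
- **Interaction.** A reader might infer that the plan claims power to detect a difference in benefit between age groups, or that it prescribes separate tests within strata. It does neither. The 0.80 refers to effects within each age category, and the subgroup model may properly be left to an analysis plan that is not shown.

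**Conclusion.** The point holds for the 65+ stratum. The 0.80 belongs to 138 completers per age category per group, and the stated recruitment does not deliver that number. With 3680 approached per group, about 40–61 and 59–82 completers aged 65+ are expected. Unadjusted power for 3.0 points is about 0.37–0.51, and the difference detectable with 80% power is about 4.2–5.1.

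This rests on the plan's flat 15% and 50% rates, on Table 1 as a stand-in for the practice lists, and on the 0–100% assumption for the 0–24 band. It is firm for the comparison group and conditional on list length for the intervention group. Neither of the two longer-list scenarios reaches 0.80 on the plan's unadjusted basis.

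It would be wrong to infer that the trial as a whole is underpowered: on the plan's inputs the whole-group comparison has about 0.98 and the younger stratum about 0.93–0.95. The overlap of the two categories at age 65 is a labelling slip with no material effect on these numbers.

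**What to change.** In Sample size considerations effect measure, replace the equal 138 per age category with the completers expected at 65+ and at 18–64 in each group, taken from the participating practices' lists. Restate the 65+ power, or the detectable difference, on that basis instead of 0.80, and say whether baseline adjustment and clustering are included. Define the strata as 18–64 and 65+.

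Because Data analysis asks whether some groups benefit more than others, base any statement that benefit differs by age on the group-by-age interaction estimate with its confidence interval, not on one stratum being significant and the other not.

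The cost is a less favourable stated figure and some rewording. No extra participants are needed.
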